### Participant timeline {13}

The participant timeline is shown in Table 2.

**Table 2 Tab2:**
[figure not shown]
Schedule of enrolment, intervention, and assessments

#### Sample size {14}

To determine sample size estimates, we used the sample size calculation method used in the previously published De Wit trial [22]. The De Wit trial sample size is based on HADS data from a longitudinal study of MND informal caregivers [4]. To test for a medium size effect (*d* = 0.5) at 5% level of significance (two-sided) with 80% power would require 64 participants in each arm (128 in total) [22]. To find an adjusted sample size “*N*” from a calculated sample size “*n*” and an estimated attrition rate “*x*”, we used the following formula: *N* = *n*/(1-*x*). We adjusted the sample size for 20% attrition to get a total sample size of 128/(1–0.2) = 160 (80 in each arm). We determined the sample size for the semi-structure qualitative interviews using recommendations for deciding saturation in theory-based interview studies [37]. We will recruit a minimum sample of 20–30 participants and 15–20 peer supporters. We will adjust the sample size using a stopping criterion of three consecutive interviews with no additional material to terminate data collection.

#### Recruitment {15}

We will use a multi-modal recruitment strategy to recruit informal caregiver participants including MND clinics, home ventilation clinics, and hospices across England, Scotland, and Wales as well as via the UK MND Association, social media, and snowballing referrals. The research team will recruit participants directly from the MND clinics of the main study site. Participant Identification Centre sites will provide study recruitment materials (recruitment flyer and the participant information sheet) to potential participants during their attendance accompanying their relative with MND to a virtual or in-person clinic appointment. Consent-to-contact will be collected from family caregivers expressing interest in participation. Interested informal caregivers will then be contacted by the central research team to explain the study, to obtain informed consent, and to collect baseline data. The MND Association and Marie Curie Charity will advertise on their websites, newsletters, and discussion forums. We will also post recruitment notices and study updates on our dedicated Twitter account. We will post trial information on other relevant forums including Health Watch-UK, healthtalk.org, and the King’s College London research volunteer newsletter. We will encourage snowballing recruitment methods. Peer supporters will be primarily recruited from the MND Association Visitors programme and other MND Association awareness campaigns.

### Assignment of interventions: allocation

#### Sequence generation {16a}

Participants will be randomised on a one-to-one basis to the intervention arm or control arm via Castor Electronic Data Capture (EDC) using a computer-generated allocation sequence based on variable block sizes (4, 6, 8) with stratification per caregiver gender (female vs other).

#### Concealment mechanism {16b}

The unblinded research officer will perform randomisation in Castor EDC and subsequently notify the participant of their group allocation. Allocation will be concealed using this computer-generated mechanism. The unblinded research officer will have no role in outcome assessment.

#### Implementation {16c}

The unblinded research officer will enter the stratification data (participant’s gender obtained from baseline demographics) into the study database hosted on the Castor EDC. The randomisation module will be used to randomise the participant. If allocated to the intervention arm, the unblinded research officer will provide the participant access to the peer support programme via the aTouchAway app and assign a peer supporter. The unblinded research officer will be the point of contact for mentors and participants in the intervention arm. If allocated to the control arm, the unblinded research officer will signpost the participant to the MND Association’s publicly available informational resources and volunteer programme. The implementation sequence is shown in Fig. 1.

**Fig. 1 Fig1:**
[figure not shown]
Flow diagram of implementation sequence

### Assignment of interventions: blinding

#### Who will be blinded {17a}

The research officer responsible for outcome assessment and the study statisticians will be blinded to group allocation. As we are unable to blind participants and peer supporters due to the nature of the intervention, we will instruct participants not to disclose their allocation status when providing outcome data over the telephone to the blinded research officer.

#### Procedure for unblinding if needed {17b}

Not applicable. Due to the low-risk nature of the intervention there will be no circumstances during the trial under which unblinding will be required.

### Data collection and management

#### Plans for assessment and collection of outcomes {18a}

Data will be collected at specified time points (see Table 2) using pre-designed case report forms over the phone, via the Qualtrics platform or postal mail depending on the participant’s stated preference. For participants who require a break during data collection over the phone, a second call will be scheduled to complete collection of data collection measures.

#### Plans to promote participant retention and complete follow-up {18b}

The main strategy to promote retention will include communication from the study team at discussion forums with participants and peer supporters. We are also offering a multi-modal strategy to provide outcome data including via emailed Qualtrics link, telephone, or postal options to improve response to outcome questionnaires. We included measurement of the HADS and ZBI at 6 weeks as another form of contact.

#### Data management {19}

We will use Castor EDC for valid data collection and secure data storage. The web-based study database will be located on a UK server, password protected and only accessible to the unblinded research officer.

#### Confidentiality {27}

In accordance with the General Data Protection Regulation (GDPR) and Data Protection Act 2018, all stored electronic data will be deidentified and stored on the password protected King’s College London server. A unique participant study number will be assigned to each participant and used on all study documents and any electronic database(s) to minimise processing of personal data. The UK Aetonix AWS cloud will store anonymised data on participant interaction with the peer-to-peer support programme (i.e. the number, duration, and type of interactions). This will be downloaded for each participant on study completion and stored in the Castor database.

Qualitative data from semi-structured interviews will be digitally recorded on an encrypted recorder and the files will be sent securely to a professional transcribing company. Electronic files of transcription will be password protected and stored on the password protected King’s College London server. Personal data used for sending questionnaires and setting up interviews will be securely destroyed on completion of study participation. Research data will be stored for 10 years. Data will be handled and stored in accordance with the 2018 Data Protection Act.

#### Plans for collection, laboratory evaluation, and storage of biological specimens for genetic or molecular analysis in this trial/future use {33}

This is not applicable as no biological specimens will be collected.

We will employ a directed content analysis approach for the qualitative analysis, as outlined by Bengtsson [38]. Summative content analysis will be performed to contextualize patterns in the data informed by the Theoretical Framework of Acceptability (TFA) [35]. Data will be coded using the seven TFA domains: affective attitude, burden, ethicality, intervention coherence, opportunity costs, perceived effectiveness, and self-efficacy.

#### Interim analyses {21b}

This is not applicable. Interim analyses will not be performed given this is a low-risk intervention study.

#### Methods for additional analyses (e.g. subgroup analyses) {20b}

We will perform a sensitivity analysis excluding data from caregivers who continue participation in the study despite death of the individual with MND for whom they provide care.

#### Methods in analysis to handle protocol non-adherence and any statistical methods to handle missing data {20c}

We will assess variables for missing data. If post randomisation variables such as intervention compliance (minimum of a once a week contact with peer supporters plus participation in a minimum of 7/12 synchronous discussion forums) are seen to predict missingness of the primary outcome, then we will consider multiple imputation using chained equations (MICE). We will assess model residuals for normality. We will perform a bootstrap analysis if the residuals (observed minus predicted value) deviate noticeably from normality. In the event of a very low intervention compliance, a complier average causal effect (CACE) analysis for the primary HADS outcome will be considered to investigate the effect on individuals who complied with the intervention. Additional sensitivity analyses addressing potential intercurrent events and non-compliance will be outlined in the statistical analysis plan.

#### Plans to give access to the full protocol, participant level-data, and statistical code {31c}

The final dataset will be available from the research team upon reasonable request. We will use the CONSORT-SPI 2018 Extension reporting guidelines [39] to ensure comprehensiveness and transparency of study findings. We will use a CONSORT-SPI flow diagram to describe participant flow through the study including the number of participants approached for enrolment, the decline rate, and the assessments to confirm eligibility and outcomes between groups. To avoid selective reporting, all outcomes will be reported as outlined in this study protocol.

### Oversight and monitoring

#### Composition of the coordinating centre and trial steering committee {5d}

The trial management group (TMG) will comprise of the chief investigator (CI), research officers, and the trial statistician team. The TMG (CI and research officers) will meet every week with the statisticians joining monthly to ensure the study is progressing according to protocol, planned timelines, and budget. The TMG will prepare a report for the trial steering committee (TSC) who will provide expert oversight and advice on all aspects of the trial.

The composition of the TSC will be based on the Medical Research Council recommendation for TSC membership and will include (1) the chief investigator (non-independent of the trial), (2) an independent chair (with clinical expertise in the field of MND and research expertise in the conduct of clinical trials), (3) an independent statistician, (4) two independent representatives one of whom is a former caregiver, and (5) a non-independent representative of the MND Association. The TSC will meet at least every 12 months to review recruitment, dropout rates, and safety data as provided by the study statistician.

The role of the TSC will include, but not limited to, the following: oversee participant rights, safety, and well-being, review regular reports of the study, assess data quality including completeness (and by so doing encourage collection of high-quality data), comment on the project analysis plan, comment on the publication policy, oversee the timely reporting of study results, monitor compliance with the protocol and any amendments, monitor compliance with previous TSC recommendations, monitor recruitment, and encourage the TMG to develop strategies to deal with any recruitment problems. Meetings will be held by videoconference unless a face-to-face meeting is deemed necessary in agreement with CI and TSC chair.

#### Composition of the data monitoring committee, its role and reporting structure {21a}

Due to the low-risk nature of the intervention we will not convene an independent Data Safety Monitoring Committee.

#### Adverse event reporting and harms {22}

As the study does not involve patients and involves a low-risk intervention (i.e. peer support programme) with informal caregivers, we do not anticipate serious adverse events as a consequence of participation in the study.

We will consider any occasion when a participant is advised by the study team or peer supporter to contact their GP as an adverse event. The research team will advise a participant to contact their GP or other relevant supports if increased psychological distress is detected with a depression and/or anxiety (cut-off of score > 10) in the HADS measured at 6 and 12 weeks or if a peer supporter raises concern.

In the event of concern about a participant, the research team may recommend the following options: (1) ask the participant if a family member or friend can be contacted for immediate support; (2) recommend the participant contact their GP for further support; and (3) recommend the participant accesses other avenues of support such as that offered by the MND Association Visitors programme or Marie Curie. Peer supporters will be advised to contact the unblinded research officer if they have concerns warranting advice to a study participant to contact a GP.

An adverse event will be documented on any occasion when a peer supporter expresses difficulty or conflict with their allocated participant that requires intervention from the research team or when a peer supporter requests to withdraw from the peer supporter role during the 12-week intervention period. Any expression of conflict or difficulty will be adjudicated in terms of required action and may include the following: (1) no need for action, informal debrief sufficient, (2) need for the unblinded research officer to reiterate to participant the expectations regarding engagement with their peer supporter, (3) reassignment to another peer supporter, and (4) discontinuation from the trial. We will also consider death of the person a participant is providing care for as an adverse event.

In the event of an SAE occurrence, it will be reported immediately and always within 24 h upon knowledge of the event to the sponsoring R&D department. We will submit SAE reports to the Main REC within 15 days of the chief investigator becoming aware of the event, using the National Research Ethics Service (NRES) template. All other AEs will be reported to the sponsor in the Annual Progress Report and included in the TSC committee report for review.

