#### Intervention description {11a}

Participants randomised to the intervention arm will be provided access to a 12-week virtual peer-to-peer support programme comprising (1) audio, video, or text private and secure one-to-one messaging with a dedicated peer supporter; (2) moderated synchronous weekly discussion forum for peer supporters and informal caregiver participants on specific topics (e.g. caregiver self-care, the emotional impact of caregiving); (3) asynchronous group chats in which participants can continue discussions and post questions; and (4) access to informational resources.

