#### Strategies to improve adherence to interventions {11c}

We will instruct peer supporters to set expectations and boundaries in terms of frequency and timing of contact in accordance with their personal preferences. We will also instruct peer supporters to contact their allocated study participant a minimum of once a week and let the research team know if no contact is received. Participants are provided the same instructions. Peer supporters will have access to a senior clinical member of the research team throughout the programme with whom they can share any concerns about themselves or their assigned participant. The research team will provide a peer supporter debriefing session every 4 weeks to give them an opportunity to discuss any issues in relation to their peer supporter role within the trial and to discuss solutions.

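### The GP-advice adverse event includes a peer supporter route that only the intervention arm has, so equal distress can produce more recorded events there; recording the source would keep this from being read as harm

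*Protocol article*

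**What the plan says.** Under Adverse event reporting and harms {22}, the protocol article states: "We will consider any occasion when a participant is advised by the study team or peer supporter to contact their GP as an adverse event". Such advice is given when a HADS anxiety or depression score exceeds 10 "in the HADS measured at 6 and 12 weeks or if a peer supporter raises concern". The reporting line for the second trigger is also set out: "Peer supporters will be advised to contact the unblinded research officer if they have concerns warranting advice to a study participant to contact a GP".

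Implementation {16c} shows who has a peer supporter. For those allocated to the intervention, the officer who randomises will "provide the participant access to the peer support programme via the aTouchAway app and assign a peer supporter". For control: "If allocated to the control arm, the unblinded research officer will signpost the participant" to public resources and the volunteer programme of the MND Association. The programme includes "private and secure one-to-one messaging with a dedicated peer supporter" (Intervention description {11a}). Contact is meant to be regular: "We will also instruct peer supporters to contact their allocated study participant a minimum of once a week" (Strategies to improve adherence {11c}).

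Two further adverse events involve peer supporters. The harms section says: "An adverse event will be documented on any occasion when a peer supporter expresses difficulty or conflict with their allocated participant" if the research team has to intervene. It treats a peer supporter's request to withdraw from the role in the same way. Non-serious events go to the sponsor's annual report and to the trial steering committee. The annual report to the ethics committee also covers adverse events. There is no independent data monitoring committee.

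**The concern.** A single event definition combines a route that both arms share with a route that one arm has. Intervention participants have someone in at least weekly contact who is told to pass on concerns that warrant GP advice. The article describes no counterpart for control participants. The MND Association volunteers to whom they are signposted have no described reporting duty to the trial.

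Caregiver distress is the main participant harm that the protocol anticipates, and the steering committee is the body that reviews safety. If it sees GP-advice events by arm with the routes combined, an intervention-arm excess could come from closer observation rather than from more distress. An apparent parity could likewise hide a reduction in distress. The stake is how the harms table is read, not the test of efficacy.

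**Working it through.** **Routes to the event, by arm**

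| Route to GP advice | Intervention | Control | Where stated |
|---|---|---|---|
| HADS-A or HADS-D above 10 at week 6 or 12 | yes | yes | {22}; HADS collected in both arms under Outcomes {12} and Data collection |
| Other study-team advice when distress is noticed | yes | yes | Criteria for discontinuing or modifying {11b}; {22} |
| Peer supporter advises, or raises a concern that leads to advice | yes | no | {22}, {16c}, {11a}, {11c} |

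**Arm size.** Sample size {14} gives 64 per arm for *d* = 0.5, two-sided 5% and 80% power. A t-test calculation gives 63.8, so 64 is reproduced. Inflation gives 128/(1 − 0.2) = 160, or 80 per arm. This point disputes none of these figures; 80 is used only as the arm size.

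**Expected counts with equal distress.** Let *p*, *s* and *q* be the expected occasions per participant from the HADS route, other study-team contact and the peer route. Because any occasion counts, the routes add:

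- control: 80(*p* + *s*)
- intervention: 80(*p* + *s* + *q*)
- excess: 80*q*, which is positive whenever *q* > 0

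**Illustration.** The documents give no value for *p*, *s* or *q*; all values here are assumptions. Setting *s* = 0 makes the ratio as large as it can be for a given *p* and *q*; any *s* > 0 pulls it towards 1.

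| *p* | Control 80*p* | Intervention, *q* = 0.05 / 0.10 / 0.20 | Ratio |
|---|---|---|---|
| 0.20 | 16 | 20 / 24 / 32 | 1.25 / 1.50 / 2.00 |
| 0.30 | 24 | 28 / 32 / 40 | 1.17 / 1.33 / 1.67 |
| 0.40 | 32 | 36 / 40 / 48 | 1.125 / 1.25 / 1.50 |

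**Counting participants instead of occasions.** Treat *p* and *q* as probabilities with independent routes. The intervention count is then 80[1 − (1 − *p*)(1 − *q*)]. For *p* = 0.40 and *q* = 0.05 it is 34.4 against 32 (ratio 1.075). For *p* = 0.20 and *q* = 0.20 it is 28.8 against 16 (ratio 1.8). If everyone flagged by a peer supporter also crosses the HADS threshold, the ratio per participant is 1.0.

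**Offset.** Suppose peer-prompted care lowers later HADS-triggered advice by δ occasions per participant. The excess becomes 80(*q* − δ). With *q* = 0.10 it is 8 at δ = 0, 4 at δ = 0.05 and 0 at δ = 0.10. The excess disappears only if each peer-sourced event prevents, on average, one HADS-triggered event.

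**After the change.** Restricting the comparison to HADS-triggered events removes *q* and *s*. At *p* = 0.30 this gives 24 against 24, instead of 32 against 24 with *q* = 0.10.

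**The case against.** The strongest reply is that nobody plans the comparison. Statistical methods {20a} does not list adverse events among its comparative analyses. The reports to the sponsor, the steering committee and the ethics committee are not described as arm comparisons, and nothing says that event types will be pooled into one total. Tabulation rules usually sit in the analysis plan or on the case report form, neither of which is shown. Recording what peer supporters notice is also good safety practice. All of this stands, and it keeps the point small. It does not remove it: the combined definition is stated in the article, not left out of it, and an analysis plan written later cannot recover a source that was not recorded when the event occurred.

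Three stronger readings are tempting, and the documents do not support them:

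- A reader might infer that a harmful effect on distress would go undetected. {20a} already plans a logistic analysis of HADS-A and HADS-D scores above 10, the same cut-off as the trigger, and total HADS is the primary outcome. Both are measured the same way in each arm.
- A reader might infer that control participants can reach this event only through HADS. {11b} lets the team advise a GP appointment for distress, with no limit to HADS visits or to one arm.
- A reader might set planned HADS assessments against weekly peer contacts and treat the result as a ratio of detection. A scored questionnaire with a cut-off and an informal conversation are not equivalent chances of detection.

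Peer supporter conflict and withdrawal are also intervention-only events, but they are defined separately and do not measure participant distress. They matter here only if they enter a total that is compared by arm.

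**Conclusion.** The point holds as a minor improvement to harms reporting. With equal distress, the recorded count of GP-advice events is expected to be higher in the intervention arm whenever the peer route produces any advice that is not fully offset by earlier care. The direction follows from the definition and from who is assigned a peer supporter. It assumes only that study-team advice outside HADS visits is about equally frequent in both arms. The size is unknown: the ratios in the working rest wholly on assumed rates, and poor adherence to weekly contact would shrink them. The efficacy conclusions are untouched.

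**What to change.** Leave the adverse event definition, the care given and staff discretion unchanged.

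1. Add one field to the adverse event form for the source of each GP-advice event: HADS at week 6, HADS at week 12, peer supporter, or other study-team contact. If the form already has such a field, only steps 2 and 3 remain.
2. Where adverse events are shown by arm, compare only the HADS-triggered events, with the number assessed at each time as denominator, and read them beside the planned analysis of HADS subscale scores above 10.
3. List GP advice sourced from peer supporters, peer supporter conflict and peer supporter withdrawal separately as intervention-arm events, outside any total compared by arm.

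The cost is one form field. HADS is already collected at both times, so no visit or questionnaire is added. The drawback is that the HADS-triggered count misses participants who do not return the questionnaire and distress that arises between assessments. It is comparable between arms only as far as questionnaire return is similar.

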#### Criteria for discontinuing or modifying allocated interventions {11b}

The study does not involve patients as participants and the intervention is considered low risk. Therefore, we do not anticipate the need to discontinue or modify the intervention itself. We do not anticipate serious adverse events resulting from the intervention; however, it is possible that participants may experience psychological distress due to their caregiving situation. In such cases, we will advise the study participant to make a GP appointment. Given the rapidly progressive nature of MND, it is feasible that a caregiver may experience death of the person for whom they provide care. In this event, we will ask the participant if they still wish to continue receiving peer support. Request to make a GP appointment and death of a care recipient will be documented as an adverse event. Peer supporters may experience difficulties or conflict with a study participant and may require reassignment. In additional, unanticipated life events may result in a peer supporter to request to withdraw from the role. We will document these events as adverse events. All peer supporters will be given the opportunity to participate in the semi-structured qualitative interviews exploring their experience as a peer supporter.

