We will collect the following endpoints at 12 weeks (programme end) from intervention arm participants only: (1) perceived usability of the peer-to-peer support programme using a 1-item 9-point Likert Scale using a Qualtrics autogenerated questionnaire link emailed to intervention participants; (2) acceptability of the peer-to-peer support programme (in a subset of intervention participants and peer supporters) via semi-structured qualitative interviews (digitally recorded and professionally transcribed) using topic guides informed by the Theoretical Framework of Acceptability (TFA) [35, 36]; and (3) usage metrics for both intervention participants and peer supporters will be downloaded from the aTouchAway platform. Usage metrics will comprise the following: (i) the frequency and type (text, audio, video) of peer-to-peer contact each week and overall for the 12-week programme; for audio and video contacts, we will also capture the duration of contact; (ii) the frequency of participation in a synchronous or asynchronous discussion forum; and (iii) discontinuation of the programme before 12 weeks and the week discontinued.

We will offer the opportunity to participate in a one-on-one telephone semi-structured interview to intervention participants and peer supporters, until we reach data saturation. Maximum variation sampling will be used to ensure a minimum of two participants representing caregiver variables including age (≤ 65; > 65), sex (male; female), and relationship to care-recipient (spouse, child, parent, other). We will offer the opportunity to participate in an interview at the end of a 12-week intervention period to study participants and peer supporters.

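### Difficulty or conflict in the peer relationship is a stated adverse event only when the peer supporter reports it; the caregiver's own report has no trigger

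*Protocol article*

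**What the plan says.** Two sections of the protocol article set the rule.

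- **Criteria for discontinuing or modifying allocated interventions {11b}** foresees the problem from one side: "Peer supporters may experience difficulties or conflict with a study participant and may require reassignment". It adds that a supporter may ask to leave because of life events, and closes: "We will document these events as adverse events".
- **Adverse event reporting and harms {22}** gives the working definition: "An adverse event will be documented on any occasion when a peer supporter expresses difficulty or conflict with their allocated participant". The rest of that sentence limits this to cases in which the trial team has to step in. The second limb is "when a peer supporter requests to withdraw from the peer supporter role during the 12-week intervention period". It continues: "Any expression of conflict or difficulty will be adjudicated in terms of required action", with four possible actions ranging from none to discontinuation from the trial.

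Section {22} names two further adverse events: advice to a participant to contact a GP, and death of the person being cared for. It says GP or other support will be advised if HADS depression or anxiety exceeds 10 at week 6 or 12, or if a supporter raises concern.

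Under Data collection, the questionnaire given only to the intervention arm covers "perceived usability of the peer-to-peer support programme using a 1-item 9-point Likert Scale", completed at week 12.

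**The concern.** The peer relationship has two parties. The caregiver is the randomised one and the supporter is a volunteer, yet the stated rule turns difficulty between them into an adverse event only when the volunteer voices it. A caregiver who tells the trial team that contact with the supporter is upsetting meets no stated trigger on that report alone.

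This bears on harms reporting and oversight. There is no independent data monitoring committee. Non-serious adverse events go to the sponsor in the annual report and to the trial steering committee, whose remit includes participant safety and well-being. If the definition hears one side only, those bodies receive an incomplete picture of how the pairings are working for participants.

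**Working it through.** No figure in the plan bears on this point, so the check is a reading of the adverse-event rules: list every stated trigger, then look for a route by which a caregiver's own report of difficulty becomes a documented event.

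**Step 1. Stated triggers in {11b} and {22}**

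| Trigger | Whose report or event | Records a relational problem raised by the caregiver? |
|---|---|---|
| Advice to contact a GP | Participant | No; records the advice |
| Difficulty or conflict needing research-team intervention | Peer supporter | No |
| Request to leave the supporter role | Peer supporter | No |
| Death of the care recipient | Participant's circumstances | No |

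None of the four is the caregiver's own report.

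**Step 2. Does the adjudication sentence widen the rule?** Read alone, "Any expression of conflict or difficulty will be adjudicated in terms of required action" does not say who is speaking. It comes directly after the supporter-based trigger, however, and concerns what action follows. One listed action is the "need for the unblinded research officer to reiterate to participant the expectations regarding engagement with their peer supporter". No listed action is a conversation about the supporter's conduct. The natural reading is that the paragraph deals with complaints from supporters.

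**Step 3. Does GP advice fill the gap?** In part. It is a real participant-side route. But the HADS prompt applies in both arms, and it does not show whether distress came from the pairing or from caregiving, the source named in {11b}. Section {22} also lists contacting a relative or friend and other support services as possible responses to concern; only the GP option matches a stated trigger.

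**Step 4. Do other sections fill it?**

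- Implementation {16c} makes the unblinded research officer the contact for intervention participants. A channel exists, but it is not tied to adverse-event documentation.
- Strategies to improve adherence {11c} gives participants the same instructions as supporters; the reporting instruction stated there concerns absence of contact. Debriefs every 4 weeks and access to a senior clinician are described for supporters.
- Outcomes {12} records dropout and its reasons as a fidelity measure. This misses caregivers who have difficulty but stay.
- The interviews reach a subset after the programme and are coded for acceptability.

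None of these makes the caregiver's report an adverse event.

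**Step 5. A further limit.** The trigger in {22} requires research-team intervention, yet the first adjudication outcome is that no action is needed. Section {11b} does not carry the condition in that form. The two sections do not state the threshold in the same way.

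**The case against.** The strongest reply is that the participant side is far from unwatched. GP advice and care-recipient death are both participant-side events, and HADS is screened at two fixed times in both arms. HADS total is also the primary outcome, so a net psychological harm from the programme would show in the randomised comparison. Intervention participants have a named contact role, the weekly forum is moderated, and supporters are trained in boundaries and risk. The article also never says its list of adverse events is complete, and it condenses a fuller protocol (version 1.2).

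Much of this stands. A reader might infer that the harms record would describe only the burden on volunteers, or that a low event count would be a mere artefact of the definition. The article does not support either: two of the four triggers concern participants. A reader might also put a number on the missed events, but no rate of relational difficulty is given, so any count would rest on an invented rate. Nor can it be said that participants are told to report nothing except absence of contact, because the content of their introduction and resource manual is not shown. Counting supporter withdrawals as adverse events is a choice the sponsor may make and is not an error.

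What the reply does not remove is the asymmetry. This is not a detail left to a longer document: the article sets out the conflict rule, with adjudication outcomes, and frames the risk from the supporter's side in both sections.

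**Conclusion.** The point holds as a one-sided rule. As written, a caregiver's own report of difficulty or conflict with the supporter is not documented as an adverse event unless GP advice or a supporter's complaint follows, and those routes do not identify the problem as one the participant raised. The count of intervention-related adverse events would be incomplete on the participant side, for an intervention arm of up to 80. By how much cannot be said.

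This assumes that the events listed in {11b} and {22} are the rule staff will follow. If the full protocol has a general adverse-event definition that takes in participant complaints, the article's wording still needs to be aligned with it. Primary and secondary efficacy inference is untouched. This is a cheap improvement to harms capture and safety oversight, not a flaw in the trial's main comparison.

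**What to change.** In both {11b} and {22}, extend the trigger to read along these lines: *when a peer supporter or a participant expresses difficulty or conflict arising from the peer relationship*. Reports would go to the unblinded research officer, who is already the intervention arm's contact, and be adjudicated by the existing process. State in the same words in both sections whether research-team intervention is a condition, and apply it equally to both parties.

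Optionally, add one yes/no item on such difficulty to the intervention-only usability questionnaire at week 12, kept away from the blinded outcome assessor.

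The cost is a short amendment, somewhat more recorded events and a little more adjudication work. The optional item adds one question to a form already being sent.
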